## Abstract

**Aims:**

Patients with chronic heart failure (CHF) struggle to follow self‐care plans, which may lead to worsening illness and poor quality of life. Burden of treatment (BoT) describes this workload and its impact on patients' lives. Suggesting the balance between a patient's treatment workload and their capability to manage it is crucial. If BoT is reduced, self‐care engagement and quality of life may improve. This article describes the SYMPACT study design and methods used to explore how symptoms and management tasks impact CHF patients' lives.

**Methods and results:**

We used a sequential exploratory mixed‐methods design to investigate the interaction between symptoms and BoT in CHF patients.

**Conclusions:**

If symptoms and BoT are intrinsically linked, then the high level of symptoms experienced by CHF patients may lead to increased treatment burden, which likely decreases patients' engagement with self‐care plans. SYMPACT may identify modifiable factors to improve CHF patients' experience.

## Introduction

Patients with chronic heart failure (CHF) often struggle to adhere to self‐care expectations.^1^ Non‐compliance with self‐care is suggested as a contributor to poor outcomes in CHF and is attributed to self‐care that is neither sufficient nor effective.^2^ Burden of treatment (BoT) is composed of dynamic states of workload (time and energy required to treat and manage a condition) and individual capacity (factors that alter ability to do work).^3^, ^4^, ^5^, ^6^, ^7^ Overwhelming treatment burden may be associated with adverse clinical outcomes.^4^, ^6^ Patient responsibility and engagement with self‐care adding to BoT are not unique to CHF.^7^ Clinical pathways and personal capacity appear to influence BoT in lung cancer and COPD.^8^ BoT appears to be exacerbated by the level of support provided by health care systems and socio‐economic disadvantages in end‐stage kidney disease.^9^ How symptoms interact with burden of treatment has yet to be investigated.

CHF is a life‐limiting syndrome, and patients experience persistent, progressive, and debilitating symptoms such as breathlessness, fatigue, and oedema, compromising their quality of life (QoL) despite optimized clinical treatment plans.^10^ Complete elimination of symptoms is unlikely, yet there are likely treatment options that could help reduce symptoms. Lower symptom burden is associated with improved functional ability and better self‐care engagement.^11^ While the theory of BoT acknowledges symptom burden, it argues that symptoms are theoretically distinct. Examination of the literature, clinical observations, and patient and public involvement (PPI) suggests that the symptoms in CHF may directly interact with BoT.^12^ In this study, possible interactions between BoT and symptom burden will be measured quantitatively and explored qualitatively through interviews, facilitating a deeper understanding of how patients with CHF experience burden of treatment. This paper outlines the design of the study: ‘How do SYMptoms and management tasks in chronic heart failure imPACT a patient's life (SYMPACT)?’ SYMPACT will examine and explore the interaction of symptoms experienced by patients with CHF with BoT. The authors will test and explore the hypothesis (aims) that symptoms are intrinsically linked with BoT; that is, patients with lower reported symptoms will report lower BoT, and patients with higher reported symptoms will report higher BoT. This will be confirmed in how patients describe their experience. The research questions are as follows: (Phase I) Is there a relationship between quantitatively measured symptoms and BoT? (Phase II) What is the perspective of patients with CHF on their experienced symptom burden and BoT? (Phase III) How do symptoms interact with BoT in CHF?

## Study design

SYMPACT is a sequential explanatory mixed‐methods study (*Figure*
*1*); this methodology promotes the exploration of results in a quantitative study.^13^, ^14^ Qualitative results expand on insights derived from quantitative results,^14^ facilitating deeper explanations of observed statistical relationships. Combining the SYMPACT study results with a qualitative literature synthesis^15^ enables the adductive analysis approach^16^ to form a conceptual model of the interaction between BoT and symptom burden in CHF.

**FIGURE 1 ehf213010-fig-0001:**
[figure not shown]
SYMPACT study design overview: flowchart illustrating the phases of SYMPACT and how they inform each other.

SYMPACT adheres to the Declaration of Helsinki and has been reviewed and approved by the University of Southampton Ethics Committee (ERGO: 41287) and the Nottingham HRA1 Research Ethic Committee, Health Research Authority (MREC: 18/EM/0339, IRAS: 247773).

### Phase I: multi‐centre survey of symptoms and burden of treatment in chronic heart failure

Phase I of SYMPACT will test the following hypothesis: symptom burden reported by CHF patients will be correlated with reported domains of BoT.

#### Design

A single time point survey using three validated questionnaires is used.

#### Participants

This is a multi‐centre study across primary and secondary care National Health Service (NHS) health trusts in the UK. English‐speaking adults with CHF (minimum of 6 months), and in the investigators' opinion are not cognitively impaired, will be invited to complete the questionnaires. Patients with heart transplant or who are receiving palliative care will be excluded.

#### Methods

Following informed consent, health information will be collected: (i) demographics (age, gender, ethnicity, marital status, and living situation), (ii) CHF characteristics [diagnosis date, aetiology, New York Heart Association (NYHA) class, ejection fraction, and clinical evaluations], and (iii) personal health information (health issues, medications, and hospitalizations).

Patients will be invited to complete three validated questionnaires: Heart Failure Symptom Survey (HFSS),^17^ Minnesota Living with Heart Failure Questionnaire (MLHFQ),^18^ and the Patient Experience with Treatment and Self‐Care (PETS).^19^
HFSS is a reliable disease‐specific evaluation of heart failure signs and symptoms.^17^ It measures the frequency, severity, and impact of 14 symptoms, where the higher score equates to more severe experience.MLHFQ captures key physical, emotional, social, and mental dimensions of QoL in a brief questionnaire.^20^ Lower scores on the MLHFQ relate to better health related QoL.PETS describes the work of illness, facilitating tools, and exacerbating factors involved in self‐care of generic chronic illness. It is a 48‐item questionnaire quantifying the patient experience of BoT across nine domains.^19^

#### Sample size

Sample size calculation is based on estimating the correlation between the above measures, to within a pre‐specified precision (as defined by the 95% confidence interval). A width of 0.2 was chosen as a balance between the practical considerations and the ability to draw useful conclusions on the observed correlations. Pearson's correlation power calculation formula^21^ suggests that a sample of size 350 will achieve this for any value of correlation.

#### Data analysis

Descriptive statistics will be used to summarize the study participants' personal, CHF, and health characteristics. Patients' questionnaire responses will be described across gender, age, number of health issues and medications, and NYHA class and according to left ventricular ejection fraction.

A scatter plot will be used to visually assess the relationship between reported symptom burden (measured by HFSS and MLHFQ) and BoT (measured by PETS); this will guide the choice of a suitable correlation tool (e.g. Pearson's or Spearman's) to summarize the relationship between the variables. Correlations will be presented with 95% confidence intervals.

An interim analysis will occur at about the halfway point. These results will be used to adapt the interview schedule, with specific probes to be used in Phase II.

#### Limitations

Limiting the sample to only three hospitals in a single county in the UK and patients who only speak English may reduce the generalizability of the results. Further, limiting the sample to CHF patients without heart transplants will ensure a focus to the generic lived experience of CHF. These limitations were thought to be reasonable owing to limited availability of translated versions of the validated questionnaires and the aim of the project.

### Phase II: semi‐structured interviews

CHF patients who complete Phase I will be invited to take part in a semi‐structured interview. The aim of this phase is to explore their experiences of living with CHF and elaborate on their questionnaire responses.

#### Design

Semi‐structured interviews will be conducted at either a health care facility or the participant's home, according to patient choice. Using the interim results of the questionnaires as probes in the interview should encourage in‐depth description of experience of BoT, thereby substantiating the results from Phase I or providing explanation for differences observed.

#### Participants

Phase I patients are eligible to participate in Phase II. Phase II will begin after the completion of the interim analysis.

#### Sampling

Sample size will be defined by data saturation when three consecutive interviews do not generate any new information.^22^ A maximum variation sampling technique will be used, ensuring that the Phase II sample is representative of the Phase I sample population.

#### Methods

Interviews will be audio recorded, and the interviewer may take field notes.

SYMPACT Phase II interview schedule is based on previous interview questions developed by other researchers interested in BoT^5^, ^23^, ^24^, ^25^, ^26^ and cover domains measured by PETS (Data *S1*: Interview schedule for Phase II). Further probing questions developed from Phase I interim results will be added to the interview schedule. Following the interview, researcher reflections on the interview will be audio recorded to promote transparency and reflexivity.

#### Data analysis

All interviews and researcher reflections will be transcribed. Field notes, where appropriate, are converted into Word documents. All participant identifiers in the interview data will be coded using their participant unique study number, assigned in Phase I.

Analysis of the interviews will follow an adapted form of Thomas and Harden's methods for thematic synthesis.^27^ With the use of NVIVO (QRS Internationals), the interview transcripts and researcher notes will be examined line by line for symptom terminology. These will form the initial nodes. Coding credibility will be achieved through member checking (PPI, clinical expert, and co‐authors).^28^ Each symptom node will be read in its context and a descriptive theme created. Finally, descriptive themes will be examined for similarities to the ‘a priori’ BoT framework. Constant comparison, reflexivity, and discussion with co‐researchers will increase rigour and trustworthiness.^29^

The a priori BoT framework incorporates the following: (1) *workload*: involving the effort required to enact tasks (technical and logistic), alter relationships (activate support and seek assistance), and evaluate outcomes of treatments (understanding and evaluation).^5^, ^23^ (2) *Individual capacity*: Encompassing an individual's abilities, their resources, and their readiness to address the workload. Including consideration of a patient's physical function, cognitive function, emotional status, socio‐economic resources, social support networks, literacy, culture, and beliefs.^6^ (3) *Impact*: Alterations to the patient's perception of self and their role. Including factors that make adhering to treatment plans more difficult.^5^, ^7^

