### Phase III: data integration

Data integration for SYMPACT was planned in the study design. The validated questionnaires used were chosen according to theoretical similarities to BoT theory (detailed in *Table*
*1*). The data from Phase I and Phase II will be integrated to inform the understanding of how symptoms interact with BoT in CHF. Symptom nodes and descriptive themes (Phase II) will be transformed through content analysis^30^ and compared with the symptom burden scores (HFSS and MLHFQ) and BoT scores (PETS) from Phase I, providing greater depth and insight to the patient experience. Through constantly comparing codes to the data,^13^ the descriptive themes will be refined and explored for points of interaction with the a priori BoT framework. This process should provide qualitative narratives to build on the statistical results from Phase I.

**TABLE 1 ehf213010-tbl-0001:** Data integration overview for SYMPACT

A priori BoT framework	Phase I (Quantitative) variable measured	Phase II (Qualitative) question theme
*Workload*		
Enact tasks	Clinical demand^a^ PETS domains^b^	What tasks are performed in managing chronic heart failure? Does anyone help with this?
Alter relationships		
Evaluate outcomes		
*Individual capacity*		
Individual's ability	Clinical characteristics^c^ Personal characteristics^d^ HFSS total score	What makes managing chronic heart failure more difficult or easy?
Resources and readiness		
*Impact*		
Alterations to self and role	MLHFQ total score HFSS interference scores^e^ PETS domains^b^	How does the work of managing chronic heart failure impact their life?
Factors influencing adherence		

^a^ Clinical demands: number of health issues, number of medications, hospitalizations within a year.

^b^ PETS domains: sub‐scores in PETS by work (e.g. medication management and attending appointment), facilitating tools, and exacerbating factors involved in self‐care.

^c^ Clinical characteristics: NYHA classification, aetiology, ejection fraction, CHF type, and years since diagnosis.

^d^ Personal characteristics: age, gender, marital status, and living situation.

^e^ HFSS interference scores: sub‐scale in HFSS that captures reported interference with physical activity and enjoyment of life.

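### Phase II coding starts from symptom terms alone, so treatment burden voiced without symptoms has no stated route into the analysis

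*Protocol article*

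**What the plan says.** The data analysis section of Phase II sets out the coding in order.

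- First, "the interview transcripts and researcher notes will be examined line by line for symptom terminology. These will form the initial nodes".
- Next, "Each symptom node will be read in its context and a descriptive theme created".
- Last, "descriptive themes will be examined for similarities to the" a priori BoT framework. The same section defines that framework under three heads: workload, individual capacity and impact.

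The Phase III section transforms the symptom nodes and descriptive themes by content analysis and compares them with the HFSS, MLHFQ and PETS scores. It then refines the themes and looks for points where they interact with the framework.

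The interviews themselves are not limited to symptoms. The Phase II methods section says that the "interview schedule is based on previous interview questions developed by other researchers interested in BoT" and that it covers the PETS domains. Table 1 lists open question themes such as "What tasks are performed in managing chronic heart failure? Does anyone help with this".

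The Introduction frames Phase II as a question about patients' perspective on both symptom burden and BoT. It notes that BoT theory treats symptoms as a separate concept, puts forward the opposing hypothesis that the two are bound together, and adds: "This will be confirmed in how patients describe their experience".

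**The concern.** The material is selected on one of the two concepts whose relation is under study. Every initial node contains a symptom, and the BoT framework meets only what those nodes produce. A patient who speaks at length about appointments, medicines or asking for help, without naming a symptom, gives evidence on BoT that the described sequence has no step to pick up.

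This matters for two of the study's aims. The Phase II question asks about BoT as well as symptoms, and the coding indexes only symptoms. The wider argument is whether BoT and symptoms are linked or separate. BoT that arises without symptoms is the evidence that would favour the separate view, and it is the kind that the coding does not select. The conceptual model of interaction described under Study design would be built on that selected material.

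**Working it through.** The point rests on no sample size, error rate or other figure, so there is no plan figure to reproduce. The check is to follow each kind of interview text through the steps that the article describes.

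**Inputs**

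1. Seed of the coding: symptom terms (Phase II, Data analysis).
2. Unit from which a theme is made: the symptom node, read in its context (same section).
3. Object to which the BoT framework is applied: the descriptive themes, not the transcripts (same section).
4. Material taken into integration: symptom nodes and descriptive themes (Phase III).
5. Safeguards named: member checking, constant comparison, reflexivity and discussion among the researchers (Phase II, Data analysis), and comparison of codes with data (Phase III). No search for negative cases is among them.

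**Tracing the text**

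| Kind of text | Enters an initial node? | Reaches the BoT framework? | What the analysis can show |
|---|---|---|---|
| Symptom and BoT together | Yes | Yes, through its theme | A link |
| Symptom, no BoT | Yes | Yes, and may match nothing | Absence of a link |
| BoT, no symptom term, but close to one | Not in its own right | Possibly, as context of the neighbouring node | BoT as a setting for a symptom |
| BoT, no symptom nearby | No stated route | No stated route | Nothing |

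**Reading the result**

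To judge whether two things go together, one needs to see each of them without the other. The second row supplies one such contrast. The fourth row would supply the other, and the described steps leave it empty. The coding is therefore one-sided: symptom without BoT is visible, BoT without symptom is not.

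**Whether Phase III fills the gap**

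It starts from the existing symptom nodes and themes and refines them. It describes no fresh coding of the transcripts for BoT. PETS scores, which measure BoT in its own right, would be set against interview data that were not coded for BoT in their own right.

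**Whether the interviews could supply the missing text**

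They could. The schedule is built on earlier BoT questions and asks openly about tasks, help, difficulty and impact. The gap lies in the coding, not in what is collected.

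**The case against.** Several arguments on the other side have weight.

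- **The nodes are called initial.** Nothing forbids later ones, each node is read in context, and codes are constantly compared with the data. This stands. A reader might infer that BoT without symptoms will never be coded, but the article does not say so. It only fails to state a route.
- **The analysis can disconfirm.** A reader might infer, especially from "This will be confirmed in how patients describe their experience", that Phase II can only agree with the hypothesis. The document does not support that. Symptom themes may match nothing in the framework, and the Phase II design section gives the interim results used as probes two purposes: "thereby substantiating the results from Phase I or providing explanation for differences observed". The sentence on confirmation is loose wording of a hypothesis, and the sentence before it speaks of testing and exploring.
- **Probing with Phase I results.** The methods section says: "Further probing questions developed from Phase I interim results will be added to the interview schedule". A reader might take this as contamination. It is normal practice in a sequential explanatory design, and the probes are added to a BoT-based schedule. It is not a fault here, and there is no need to restrict corroboration to unprompted text.
- **Phase I measures BoT regardless of symptoms.** This also stands: a patient with few symptoms and high PETS scores weakens the Phase I correlation. But that is evidence from patient-level scores. It does not show what BoT without symptoms consists of. Nor does it show that a patient with many symptoms may carry burden that has nothing to do with them.
- **A question about how symptoms interact with BoT may start from symptoms.** That is fair for Phase III taken alone. It does not cover the Phase II question, which names both concepts.
- **The article is condensed.** The full protocol is not shown and may contain a BoT pass. However, the article states its coding sequence step by step, so the point concerns a stated method and not an omitted detail.

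**Conclusion.** The point holds in a limited form. As described, Phase II coding is selective toward symptom-linked BoT and cannot show how much BoT patients voice without symptoms. The study can therefore answer its Phase II question only in part, and it cannot fairly weigh its hypothesis of a link against the theoretical position that symptoms and BoT are separate.

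No numerical size can be given. The article plans no co-occurrence statistic for interview text and gives nothing from which to estimate the share of BoT talk that is free of symptom terms. Any percentage would be invented.

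The conclusion assumes that the coding is carried out as the article sets it out, with no further BoT pass in a fuller document. Phase I is not affected. The change is worth making because the selection bears on the central question and is cheap to remove.

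**What to change.** Add a second line-by-line coding pass of all transcripts against the a priori BoT framework (workload, individual capacity, impact), made independently of any symptom term. Keep the symptom pass as it is. Then:

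- report the overlap between the two code sets;
- report both kinds of negative case, BoT without symptom and symptom without BoT;
- carry both code sets into the Phase III comparison with HFSS, MLHFQ and PETS.

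The framework is already defined in the Phase II data analysis section, and the transcripts, software and team stay the same. The cost is extra coding time. The interview schedule and the probes need no change. If the full protocol already contains such a pass, one sentence saying so would be enough.

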### Phase III: data integration

Data integration for SYMPACT was planned in the study design. The validated questionnaires used were chosen according to theoretical similarities to BoT theory (detailed in *Table*
*1*). The data from Phase I and Phase II will be integrated to inform the understanding of how symptoms interact with BoT in CHF. Symptom nodes and descriptive themes (Phase II) will be transformed through content analysis^30^ and compared with the symptom burden scores (HFSS and MLHFQ) and BoT scores (PETS) from Phase I, providing greater depth and insight to the patient experience. Through constantly comparing codes to the data,^13^ the descriptive themes will be refined and explored for points of interaction with the a priori BoT framework. This process should provide qualitative narratives to build on the statistical results from Phase I.

**TABLE 1 ehf213010-tbl-0001:** Data integration overview for SYMPACT

A priori BoT framework	Phase I (Quantitative) variable measured	Phase II (Qualitative) question theme
*Workload*		
Enact tasks	Clinical demand^a^ PETS domains^b^	What tasks are performed in managing chronic heart failure? Does anyone help with this?
Alter relationships		
Evaluate outcomes		
*Individual capacity*		
Individual's ability	Clinical characteristics^c^ Personal characteristics^d^ HFSS total score	What makes managing chronic heart failure more difficult or easy?
Resources and readiness		
*Impact*		
Alterations to self and role	MLHFQ total score HFSS interference scores^e^ PETS domains^b^	How does the work of managing chronic heart failure impact their life?
Factors influencing adherence		

^a^ Clinical demands: number of health issues, number of medications, hospitalizations within a year.

^b^ PETS domains: sub‐scores in PETS by work (e.g. medication management and attending appointment), facilitating tools, and exacerbating factors involved in self‐care.

^c^ Clinical characteristics: NYHA classification, aetiology, ejection fraction, CHF type, and years since diagnosis.

^d^ Personal characteristics: age, gender, marital status, and living situation.

^e^ HFSS interference scores: sub‐scale in HFSS that captures reported interference with physical activity and enjoyment of life.

